**Methods:**

A quasi-experimental design with repeated observations, taken at baseline, post-intervention, and at one and three months post-intervention, in people hospitalized with cognitive disorders or dementia. The study will be carried out in four general hospitals in Spain and will include 430 PwD and their caregivers. The intervention was previously developed using the Balance of Care methodology where nurses, physicians, social workers and informal caregivers identified the best practices for this specific care situation. We aim to personalize the intervention, as recommended in the literature. The study has an innovative approach that includes new technologies and previous scientific evidence. Valid, reliable instruments will be used to measure the intervention outcomes. Quality of care and comorbidity will be analyzed based on the use of restraints and psychotropic medication, pain control, falls, functional capacity and days of hospitalization. Continuity of care will be measured based on post-discharge emergency hospital visits, visits to specialists, cost, and inter-sectorial communication among healthcare professionals and informal caregivers. Statistical analysis will be performed to analyze the effect of the intervention on quality of care, comorbidity and continuity of care for patients with dementia.

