## Statistical analysis

Descriptive analysis will be used for baseline data. Categorical variables will be represented with absolute frequencies and percentages. For continuous variables, mean values, standard deviation or medians will be calculated. To study the effect of the intervention, analysis of co-variance will be carried out (ANCOVA), with Student’s t-test for continuous variables and McNemar’s test for categorical variables. Sensitivity will be analyzed to compare basal data of participants who complete the study with those who do not. Main outcome measures include quality of care and comorbidity (physical restraints, psychotropic medication, falls, functional capacity, pain assessment, length of hospital stay and number of readmissions); continuity of care (informal caregiver reaction, multidisciplinary and intersectoral communication) economic costs of hospital and community care and nurses’ level of knowledge in acute care of PwD. Outcomes measured will assess longitudinal changes from all the collection phases; baseline (admission), discharge, 1 month and 3-month follow-up, comparing pre-intervention and post-intervention values. Confidence intervals of 95% will be calculated. Values of *p* < 0.05 will be considered significant. Statistical analysis will be performed with R-3.2.3. for Windows. The research team will reflect on the analyzed data and issue a final report including the CARExDEM program with the required modifications identified following the implementation evaluation. This will ease the subsequent implementation of the program in other hospitals.

For the sample calculation, we estimated that a sample of 432 participants need to be included in the study, assuming an improvement in patients with pain around 50%, with precision of 5%, a confidence interval of 95 and 10% of dropouts. Only the research team and data manager will have access to data.

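### The 5% precision behind the 432 fits one proportion in all patients pooled; for the two-group comparison the 95% half-width is about 10 points

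*Protocol article*

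**What the plan says.** The sample-size text is in the last paragraph of Statistical analysis in the Protocol article: "we estimated that a sample of 432 participants need to be included in the study", on the basis of "assuming an improvement in patients with pain around 50%, with precision of 5%, a confidence interval of 95 and 10% of dropouts". The section gives no control-group rate, no between-group difference and no power.

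Setting and participants, with Table 1, divides the total into a control group under usual care and an experimental group receiving CARExDEM. Each has 54 patients in each of four hospitals, so 216 per group and 432 in all. The two groups are different patients, recruited one after the other.

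Statistical analysis says the effect of the intervention will be studied by comparing values before and after its introduction, with 95% confidence intervals and a 0.05 significance threshold.

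**The concern.** One proportion, a precision and a confidence level are the ingredients for estimating a single percentage in a single sample. The study's question is a difference between two groups, each half the size of that sample. Halving the sample widens the interval for each group, and subtracting two independent estimates widens it again. A precision figure computed for the whole therefore does not carry over to the comparison.

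This matters because it is the only sample-size rationale in the article. A reader would naturally take 5% as the resolution with which the intervention effect on pain will be known.

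**Working it through.** **Inputs.** From Statistical analysis: p about 0.50, precision d = 0.05, 95% confidence (z = 1.96), dropout 10%. From Table 1: 8 cells (4 hospitals × 2 groups) of 54.

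**1. Reproducing 432.** One-sample precision formula, n = z²p(1−p)/d²:
- 1.96² × 0.25 / 0.05² = 384.2, so 385 evaluable.
- 385 / 0.90 = 427.8, so 428 recruited.
- 428 / 8 = 53.5, so 54 per cell; 8 × 54 = 432.

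The stated total and the Table 1 cells both follow. As a check on the alternative, two-proportion calculations (two-sided 5%, 80% or 90% power, with and without continuity correction, 10% dropout) give these totals:
- 50% vs 25%: 130 to 190.
- 50% vs 40% or 60%: 864 to 1,196.
- 50% vs 45% or 55%: 3,478 to 4,744.

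None gives 432. A pair such as 20% vs 10% at 80% power comes close (444), but the article states no such rates, and that calculation has no precision input.

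**2. Where the 5 points hold.** All groups pooled: 432 × 0.9 = 388.8 evaluable, and 1.96 × √(0.25/388.8) = 0.0497, or ±5.0 points.

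**3. What the design delivers.** Per group, 216 × 0.9 = 194.4, so about 194 evaluable. Assume p = 0.50 in each group.
- One group: 1.96 × √(0.25/194) = 0.070, or ±7.0 points.
- Difference: 1.96 × √(0.25/194 + 0.25/194) = 0.0995, or ±9.95 points.
- Difference with no dropout (216 per group): ±9.4 points.
- Difference at 50% vs 25%: 1.96 × √((0.25 + 0.1875)/194) = 0.093, or ±9.3 points.

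**4. Power with 194 per group, control rate assumed 50%, two-sided 5%.** Power = Φ{[Δ√n − z√(2p̄(1−p̄))] / √(p₁(1−p₁) + p₂(1−p₂))}, where p̄ is the mean of the two rates.

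| Difference | Power |
|---|---|
| 5 points | 16% |
| 10 points | 51% |
| 14 points | 80% |
| 25 points (halving) | over 99% |

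**5. What 5 points would take.**
- On the difference: 1.96² × 0.50 / 0.05² = 768.3, so 769 evaluable per group; 769 / 0.9 gives 855 recruited per group, 1,710 in total.
- Within each group separately: 2 × 428 = 856 in total.

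Clustering by hospital is ignored throughout.

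**The case against.** **The formula is inferred.** The article does not name it, nor does it say that the 5% refers to a difference. That is correct, and the point is worded accordingly. The inference is strong because the inputs lead to the stated total and to the cell size.

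**Nothing is miscalculated.** A reader might infer an arithmetic error. There is none: the total agrees with its inputs. The fault is that the justification does not match the comparison.

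**Some circumstances would give ±5.** Solving 1.96 × √(2p(1−p)/194) = 0.05 gives a pain prevalence of about 7% in both groups, against the stated figure of around 50%. Adjustment by ANCOVA would need covariates explaining about 75% of the variance, since (0.05/0.0995)² is about 0.25. Neither is impossible, but the article supports neither. Pairing cannot help, because the groups are different people.

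**The study may be large enough.** A reader might infer that it is underpowered or needs 1,710 patients. The article does not support that. The stated improvement could mean that half the patients improve, that pain is halved, or that half have pain. If it means a fall from 50% to 25%, power exceeds 99%. The 1,710 applies only if ±5 on the difference is really wanted.

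**A null result will not necessarily be over-read.** The planned 95% intervals will show what the data exclude, so the harm lies in the planning claim rather than in the eventual estimate.

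**Side issues.** The 54 in every column of Table 1 can be read as the cohort scheduled at each collection, so it is not an error. The Abstract's "will include 430 PwD and their caregivers" against 432 elsewhere is a clerical mismatch with no bearing here.

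**Conclusion.** The concern holds as a mismatch between the sample-size justification and the design. The stated 5% precision applies to one proportion estimated in control and experimental patients together, a quantity that answers none of the objectives. For the between-group difference the half-width is about 10 points, twice the stated figure, and for either group alone it is about 7.

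These sizes rest on 10% dropout, independent groups, about 50% with the outcome in each group, no covariate adjustment and no clustering. They are not sensitive to the reading of the 50%: the half-width for the difference stays at 9.3 points if the rates are 50% and 25%. Power is sensitive to it, so no conclusion about adequacy of the sample follows until the control rate and target difference are stated.

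**What to change.** Keep 432. Remove the 5% precision as the basis for the comparison and replace it with a statement such as:

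> 216 per group (about 194 evaluable after 10% dropout) gives a 95% confidence interval of about ±10 percentage points for the between-group difference in the proportion with pain, assuming about 50% in each group. Under an assumed control rate of 50%, power is about 80% for a 14-point difference and about 51% for 10 points (two-sided 5%).

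The 14 points is a consequence of the sample size, not a target found in the article, and should be presented that way. The authors should add the control rate and the difference they meant by an improvement of around 50%, and note that the figures make no allowance for clustering by hospital. The 430 in the Abstract can be changed to 432 at the same time.

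The cost is wording only: no extra patients and no change to data collection. The stated precision becomes less favourable. At the time of the article, Study progress reports 173 controls recruited and the intervention still in preparation, so the basis could have been restated before any experimental-group results.

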## Study progress

Data collection for the control group started in July 2018 and is ongoing. So far, 173 patients have been recruited in control group. Multidisciplinary groups are currently working on the intervention at each hospital, following the BoC methodology.

## Discussion

This paper presents the study protocol for the CARExDEM program. This intervention aims to provide nurses with strategies for the management of PwD in acute care and to raise awareness of the importance of individualized care in these patients to improve continuity of care in exacerbated situations in PwD. Hospitals in Spain are still far from being environments prepared for PwD. Most focus on quick and efficient diagnosis and management of acute serious disease processes, whereas other countries are now restructuring their units to be more senior friendly.

The presentation of the comprehensive CARExDEM care management protocol for PwD is innovative as we have found no published interventions for these patients in hospital settings. There is a need to ensure continuity of care so patients can return to their setting with minimal disruption. Informal caregivers will also benefit from a smoother transition after hospital discharge.

The main limitation of the study is its scope of application. As it is a study carried out in specialized units, the results obtained cannot be generalized to the other wards in the hospital. To compensate this limitation, we have included 4 hospitals from different Autonomous Communities to broaden project development in different clinical settings. A strength of this study is the information that contributes to empowering patients, their caregivers and professionals and encourages policy-makers and organizations to adapt hospital settings to the needs of PwD.

## Data Availability

The data that support the findings of this study are available on request from the corresponding author, (AZ).

## Abbreviations

ADL: Activity of daily living
BoC: Balance of Care
CARExDEM: Care of persons with cognitive impairment or dementia hospitalized in acute hospitals
CHN: Complejo Hospitalario de Navarra
CRA: Caregiver reaction assessment
IC: Informal caregiver
IEXPAC: Instrument for evaluation of experience of Chronic Patients
HCB: Hospital Clinic Barcelona
HPH: Hospital Puerta Hierro Madrid
HMV: Hospital Marqués de Valdecilla
MNA: Mini-nutritional assessment
NPI-Q: Neuropsychiatric Inventory Questionnaire
OCDE: Organization for Economic Cooperation and Development
PARIHS: Promoting Action on Research Implementation in Health Services
PAINAD: Pain assessment in advanced dementia
PwD: Patient with dementia
PSS: Patient Satisfaction Scale
RTPC: RightTimePlaceCare Study
SPMSQ: Short Portable Mental Status Questionnaire
RUD: Resource utilization in dementia
